## Abstract

***Background*:** Hypertriglyceridemia, is commonly found in patients with diabetes. Xuezhikang, an extract of red yeast rice, is effective in reducing cardiovascular events in Chinese patients with diabetes and coronary heart disease (CHD). Xuezhikang has been reported to significantly decrease the level of triglycerides (TG), a potential causal risk factor for myocardial infarction. On the basis of a similar reduction in low-density lipoprotein cholesterol, this study will evaluate the effect of xuezhikang on TG levels compared with pravastatin in patients with type 2 diabetes mellitus (T2DM) and dyslipidemia.

***Methods*:** This is an open-label, multicenter, randomized controlled study to assess the effects of xuezhikang (1.2 g/day) and pravastatin (20 mg/day) on TG and other blood lipid parameters in patients with T2DM and dyslipidemia. A total of 114 patients will be enrolled and randomly assigned 1:1 to receive xuezhikang or pravastatin treatment for 6 weeks.

***Results*:** The primary outcome measure is the change from baseline in fasting TG levels after 6 weeks. The change from baseline in other fasting and postprandial lipid parameters, and glucose profiles at 1, 2, and 4 h after a nutritious breakfast will also be explored.

***Conclusion*:** This study will evaluate the effect of a 6-week treatment with xuezhikang compared with pravastatin on fasting and postprandial TG levels and other blood lipid parameters in patients with T2DM and dyslipidemia without atherosclerotic cardiovascular disease (ASCVD). The results will provide more information on optimizing the lipid control of patients with diabetes in the primary prevention of ASCVD.

***Trial Registration*:** Chinese Clinical Trial Registry, ChiCTR2100046704. Registered 27 May 2021.

## INTRODUCTION

1

Type 2 diabetes mellitus (T2DM) is an independent risk factor of atherosclerotic cardiovascular disease (ASCVD) [1, 2], and has been regarded as an equivalent risk of coronary heart disease (CHD). Diabetes is often associated with a particular lipid spectrum, characterized by an increase in triglycerides (TG) and small dense low-density lipoprotein cholesterol (LDL-C), and a decrease in high-density lipoprotein cholesterol (HDL-C) [3], which makes treating diabetes more complicated. For patients with T2DM, controlling LDL-C levels is the first goal of lipid-lowering therapy for both primary and secondary prevention [4]. Elevated TG levels, especially in the postprandial state, increases ASCVD risk for patients with diabetes [5, 6]. The second goal is to control non-HDL-C levels, which is important for patients with diabetes [7]. Non-HDL-C includes the cholesterol content of nearly all atherosclerotic lipoproteins, including LDL, lipoprotein (a) [Lp(a)], and TG-rich lipoproteins and their remnants [8].

At present, statins are the cornerstone of cholesterol control in patients with diabetes [9]; however, the effects of statins on TG levels varied in previous studies. Rosuvastatin has been reported to reduce TG levels by 12-37% across a dose range of 5-20 mg/day [10]. The TG reduction of atorvastatin ranged from 11.6% for 2.5 mg/day to 32.15% for 80 mg/day [11]. Xuezhikang, a polypill extracted from red yeast rice, contains 13 kinds of natural statins, including lovastatin and its homologues, as well as unsaturated fatty acids, ergo sterol, flavonoids, and other active ingredients [12, 13]. Another study reported that non-statin elements of xuezhikang may have synergistic effects in improving blood lipids and inhibiting the synthesis of TG [14]. Xuezhikang was also effective in the reduction of cardiovascular events, including myocardial infarction and CHD death, in Chinese diabetic patients with CHD [15, 16]. Interestingly, xuezhikang significantly decreased fasting TG levels in addition to LDL-C in Chinese patients with T2DM [17]. Moreover, xuezhikang was shown to be beneficial in the treatment of postprandial hypertriglyceridemia after a high-fat meal in patients with CHD without T2DM [18]. Considering that high TG levels, especially in the postprandial state, are a causal risk factor for myocardial infarction [19], lowering TG levels may contribute to the reduction of ASCVD risk in patients with diabetes.

It has been reported that xuezhikang 1.2 g/day or pravastatin 20 mg/day reduced the LDL-C level by a similar extent, about 24-28% [12, 20-23]. Given that both xuezhikang and pravastatin reduce LDL-C, similarly, our study compares the clinical benefit and safety of both xuezhikang and pravastatin in patients with T2DM and dyslipidemia without ASCVD, in terms of TG reduction in the fasting and postprandial states.

## MATERIALS AND METHODS

2

### Study Design

2.1

This is an open-label, multicenter, prospective, randomized controlled study to evaluate the effects of xuezhikang (1.2 g/day) and pravastatin (20 mg/day) on TG levels and other blood lipid parameters for 6 weeks in patients with T2DM and dyslipidemia (study protocol version 4.0, dated 13 Jan 2021). Pravastatin is used as a comparator in this study as previous studies have shown that the magnitude of LDL-C reduction of pravastatin and xuezhikang at current dosages were similar [12, 20]. The clinical trial registration number (ChiCTR2100046704) can be found at http://www.chictr.org.cn.

Patients with T2DM and dyslipidemia will be enrolled and randomly assigned (1:1) to xuezhikang or pravastatin therapy in 3 centers in China. Sealed envelopes with a red card or a white card, representing the experimental group (xuezhikang) and the control group (pravastatin), respectively, will be used to allocate the treatment arm. Blood lipids at fasting and 1, 2, and 4 h after a nutritious breakfast will be monitored at baseline and 6 weeks after treatment. Only drugs affecting lipid metabolism will be prohibited during the trial. Treatment will be discontinued because of withdrawal by patient for any reasons or decision by the investigator for safety reasons.

### Patient Population

2.2

Eligible patients must meet the following criteria before entering this study.

### Inclusion Criteria

2.3

Aged ≥ 18 years.Diagnosed with T2DM and dyslipidemia. T2DM should be diagnosed according to American Diabetes Association Standards of Medical Care in Diabetes (2020) [24]. Dyslipidemia should be diagnosed according to the test within 4 weeks, and both of the following conditions should be met: (1) Fasting TG ≥1.7 mmol/L and <5.6 mmol/L; (2) Fasting LDL-C ≥1.8 mmol/L and <4.9 mmol/L.Patients should have at least one of the following risk factors: (1) T2DM duration ≥10 years; (2) Smoking; (3) Obesity (body mass index ≥28 kg/m^2^, or waist circumference ≥90 cm [male] or ≥85cm [female]); (4) Hypertension; (5) Fasting HDL-C <1.0 mmol/L or LDL-C ≥2.6 mmol/L within 4 weeks.

### Exclusion Criteria

2.4

Known ASCVD including CHD, ischemic stroke, transient ischemic attacks, peripheral artery disease, etc.Use of lipid-lowering drugs within 3 months prior to enrollment.Uncontrolled diabetes with HbA1c ≥8.0%.Active liver disease or dysfunction including sustained serum transaminase elevation of unknown reason or higher than three-fold of the upper limit of normal.Known myopathy or serum creatine kinase >5-fold of the upper limit of normal not caused by muscle injury.Contraindication to xuezhikang capsules, pravastatin, long-term use of glucocorticoids or contraceptives.At the acute stage of infectious diseases, or with any one of the following diseases: hyperthyroidism, hypothyroidism, acute cerebrovascular disease, severe cardio-renal insufficiency (glomerular filtration rate <60 mL/min/1.73m^2^), malignant tumor, hematopoietic disease, autoimmune disease, digestive system disorders affecting digestion and/or absorptive function, mental disorder, other severe or unstable physical disease.A history of alcohol or drug abuse or dependence within 3 months before inclusion in the trial.Participation in clinical trials of other drugs within 3 months before inclusion in the trial.Other conditions that make it inappropriate for participation at the investigator's discretion.

### Enrollment Schedule

2.5

This study consists of four visits: screening period, run-in period, before and after the 6-week treatment (Fig. **1**). Patients will be screened for study eligibility (Visit 1). After screening, health education and diet instructions will be given to eligible patients. Briefly, they are suggested to follow a low-fat, low-salt diet, and avoid alcohol and strenuous exercise. Patients will be requested to follow the instructions for at least 14 days. No lipid-lowering drug is allowed during this period. After a 14-day run-in period, patients will receive blood lipid tests and safety assessments (Visit 2). Eligible patients will be randomized to receive xuezhikang or pravastatin. A nutritious breakfast with a total of 800 kcal will be given as described previously [12], followed by blood lipid tests at fasting and 1, 2, and 4 h after breakfast (Visit 3). Patients will be assessed again after 6 weeks of treatment. (Visit 4).

### Outcome Measures

2.6

The primary outcome measure is the change from baseline in fasting TG levels after 6 weeks of xuezhikang (1.2 g/day) and pravastatin (20 mg/day). The secondary outcome measures are change from baseline after 6 weeks of treatment in other fasting lipid indexes (including total cholesterol, LDL-C, HDL-C, non-HDL-C, remnant cholesterol, Lp(a), apolipoprotein [Apo] A1, and ApoB), change from baseline in postprandial TG levels 1, 2, or 4 h after breakfast, fasting, and postprandial plasma glucose and insulin levels, fasting HbA1c level, and change from baseline after 6 weeks in fasting and postprandial levels of high-sensitivity C-reactive protein. An overview of the assessments is provided in Table **1**.

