### Statistical Analysis

2.9

The analysis of covariance will be performed on the primary endpoint with last observation carried forward for missing values, as well as on the secondary efficacy parameters. All statistical tests between treatment groups will be tested at the 2-sided <0.05 significance level. Descriptive statistics will be performed on the safety outcomes. Two analysis sets will be used for the statistical testing: the full analysis set, including all randomized patients with baseline and at least one post-baseline data, and the per-protocol analysis set, including all randomized patients completing the study without major protocol deviations.

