## RESULT AND DISCUSSION

3

To our knowledge, this is the first randomized controlled trial to compare the TG lowering effect of xuezhikang and a synthetic statin, pravastatin, in the fasting and postprandial states of patients with T2DM and dyslipidemia without ASCVD. Xuezhikang is a lipid-lowering agent that has been proven to reduce cholesterol levels and incidence of cardiovascular events, as well as overall mortality in Chinese patients with CHD in several studies [15, 25, 26]. A systematic review and meta-analysis study that included 16 randomized clinical trials with treatments over 8 weeks showed that xuezhikang significantly reduced fasting TG levels in addition to other lipid parameters in patients with T2DM, compared with statins [17]. However, all the trials included in this systematic review were conducted in China and most of them were published in journals written in Chinese, which are not accessible to the global community, in particular, the design and methodology. More importantly, postprandial TG levels were never explored in those studies. With that in mind, our study design is planned to address the shortcomings in current studies as mentioned above.

TG control may be interrupted by fasting glucose levels [27, 28], therefore, in the present study, patients with well-controlled glucose, confirmed during the first two visits, will be enrolled. In the initial screening and after a 14-day run-in period, patients with HbA1c ≥8.0% or who have switched hypoglycemic drugs will be excluded. All patients included in this study have been diagnosed with T2DM and dyslipidemia, without ASCVD, and require primary prevention. According to Chinese guidelines for the management of dyslipidemia in adults [29], moderate-intensity statin treatment is recommended as first-line lipid-lowering therapy to reduce the risk of ASCVD. Xuezhikang (1.2 g/day) is qualified as a moderate-intensity statin (defined as LDL-C reduction of 25 to <50%) for primary ASCVD prevention in patients with T2DM [29]. Patients with very high ASCVD risk are not included in this study, as the target of LDL-C control is higher, <1.4 mmol/L and even lower [30], for which intensive statins and/or the combination of other cholesterol-lowing drugs may be recommended as the initial therapy [31, 32]. Subjects will be recommended to receive a combination therapy, such as a statin and ezetimibe, if they fail to achieve the LDL-C goal after the 6-week of monotherapy.

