Lp(a), similar in structure to LDL, is an atherogenic lipoprotein, and a high Lp(a) level is related to an increased residual ASCVD risk [42, 43]. Although the therapeutic target of Lp(a) has been proven to be difficult, several medicines, including proprotein convertase subtilisin/kexin 9 inhibitors (PCSK9i), have shown their effects in Lp(a) reduction [44]. PCSK9i may reduce Lp(a) concentration by enhancing its clearance and reducing its production [45, 46]. A pharmacological study showed the combination of xuezhikang and ezetimibe significantly attenuated the increase in PCSK9 level, resulting in the marked upregulation of LDL receptors, which may explain the role of xuezhikang in Lp(a) regulation [47]. The fasting Lp(a) is designed as an exploratory outcome in this study to investigate the effect of xuezhikang on the Lp(a) level. It is worth noting that the new onset of diabetes risk is a potential side effect in patients taking statins [48]. A retrospective study of red yeast rice prescriptions in Taiwan showed that xuezhikang has a lower risk in the new onset of diabetes than lovastatin, the rates of diabetes were 1.01 and 2.59 per 100 person-years, respectively [49]. To explore the impact of xuezhikang and a synthetic statin on glucose profile, fasting and postprandial glucose and insulin levels, and HbA1c level are assessed as the secondary objectives.

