## Figures and Tables

**Fig. (1) F1:**
[figure not shown]
Study design. **Abbreviations:** T2DM, type 2 diabetes mellitus; V, Visit.

**Table 1 T1:** Study plan.

**Visits**	**Visit 1**	**Visit 2**	**Visit 3**	**Visit 4**
Time point (day)	-14	-1	0	42
Informed consent	×			
Inclusion/exclusion criteria	×	×		
Randomization			×	
Dietary guidance	×	×	×	×
Demographic data	×			
Previous medical history	×	×		
Physical examination	×	×	×	×
Nutritious breakfast			×	×
Fasting blood lipid routine (TC, TG, HDL-C, LDL-C)		×		
Fasting HbA1c levels		×		×
Blood lipids complete set (TC, TG, HDL-C, LDL-C, non–HDL-C, RC, Lp(a), Apo A1, ApoB) at fasting and 2 and 4 h after the meal, blood lipid routine (TC, TG, HDL-C, LDL-C) at 1 h after the meal			×	×
**High sensitivity** C-reactive protein at fasting and 2 and 4 h after the meal			×	×
Insulin levels at fasting and 1 and 2 h after the meal			×	×
Plasma glucose levels at fasting and 1 and 2 h after the meal			×	×
Blood routine, urine routine, urine pregnancy test (for fertile women)		×		×
Creatine kinase		×		×
Hepatic function test		×		×
Renal function test		×		×
Electrocardiogram		×		×
**Health education and diet instructions**			×	
×	×		×	×
Record adverse events	×	×	×	×
Distributing a snack containing carbohydrate before leaving hospital			×	×
Distributing drugs and log cards			×	
Retrieving drugs and log cards				×

**Abbreviations:** TG, triglycerides; TC, total cholesterol; HDL-C, high density lipoprotein cholesterol; LDL-C, low density lipoprotein cholesterol; non-HDL-C, non-high density lipoprotein cholesterol; RC, remnant cholesterol; Lp(a), lipoprotein (a); Apo A1, Apolipoprotein A1; ApoB, Apolipoprotein B.

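### The insulin outcomes are compared without regard to insulin treatment, so injected and own insulin may be mixed; a restriction by baseline use is a cheap improvement

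*Protocol article*

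**What the plan says.** **Outcome.** Section 2.6 makes "fasting, and postprandial plasma glucose and insulin levels, fasting HbA1c level" part of the secondary outcome list. Table 1 schedules "Insulin levels at fasting and 1 and 2 h after the meal" at Visits 3 and 4. C-peptide is not in the table.

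**Purpose.** Section 3, after discussing statins and new-onset diabetes, states: "To explore the impact of xuezhikang and a synthetic statin on glucose profile, fasting and postprandial glucose and insulin levels, and HbA1c level are assessed".

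**Who can enter.** Neither section 2.3 nor section 2.4 mentions insulin therapy. The glycaemic exclusion in 2.4 is "Uncontrolled diabetes with HbA1c ≥8.0" per cent. Section 3 adds that, at screening and after the run-in, "patients with HbA1c ≥8.0% or who have switched hypoglycemic drugs will be excluded"; this removes patients who changed treatment, not those on a stable one. One of the five alternative qualifying risk factors in 2.3 is "T2DM duration ≥10 years". For the treatment period, section 2.1 says: "Only drugs affecting lipid metabolism will be prohibited during the trial".

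**Analysis.** Section 2.9 sets one method for primary and secondary efficacy measures alike: "The analysis of covariance will be performed on the primary endpoint with last observation carried forward for missing values, as well as on the secondary" ones. The full analysis set and the per-protocol set are defined by available data and by protocol adherence. Neither refers to insulin use.

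**The concern.** Insulin adds to glucose and HbA1c in describing a drug's glycaemic effect mainly when it reflects the patient's own response. In an insulin-treated patient, a fasting, 1 h or 2 h value may also depend on the injected product, its dose and the time since injection. If such patients are pooled with the rest, part of the sample carries little or none of the signal and may add variance.

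The risk is a masked difference: a null insulin result would be hard to read, because it could mean either no drug effect or a diluted comparison. Only the secondary insulin outcomes are at stake.

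**Working it through.** **1. The plan's own figure.** The article gives no calculation for insulin. Its sample size (2.8) concerns fasting triglycerides: difference 0.46, SD 0.66, two-sided 0.05, power 90%. The exact two-sample t calculation gives power 89.8% at 44 and 90.5% at 45 per arm, so 45 per arm. With 20% dropout, 45 / 0.8 = 56.25, rounded up to 57 per arm, and 2 × 57 = 114. This reproduces, and it neither supports nor weakens the insulin point.

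**2. Can insulin-treated patients enter and be analysed?** Reading 2.1, 2.3, 2.4 and section 3 together: no criterion bars them, stable glucose-lowering treatment is accepted, and only lipid-affecting drugs are prohibited. Nothing in 2.9 separates them. So yes, on the rules as published.

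**3. Information kept by pooling.** Assumptions, none of them in the article:
- f = share of insulin users, equal in both arms;
- k = SD in users divided by SD in non-users (for the adjusted change);
- a treatment effect d, in non-user SD units, present only in non-users.

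Pooled: mean difference (1 − f)d, SD √[(1 − f) + f k²], n per arm. The small extra variance from mixing two means is ignored. Restricted to non-users: difference d, SD 1, (1 − f)n per arm.

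The ratio of squared signal-to-noise, pooled over restricted, is (1 − f)² / [(1 − f) + f k²] ÷ (1 − f) = (1 − f) / [(1 − f) + f k²].

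| f | k = 1 | k = 2 | k = 4 |
|---|---|---|---|
| 10% | 0.90 | 0.9/1.3 = 0.69 | 0.9/2.5 = 0.36 |
| 20% | 0.80 | 0.8/1.6 = 0.50 | 0.8/4.0 = 0.20 |
| 30% | 0.70 | 0.7/1.9 = 0.37 | 0.7/5.5 = 0.13 |

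**4. The same on the power scale.** For illustration take 45 evaluable per arm and d = 0.46/0.66 = 0.697 SD, borrowed from the triglyceride calculation, so that power is 90.5% with no users.

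| f | pooled, k = 1 | pooled, k = 2 | non-users only (n per arm) |
|---|---|---|---|
| 10% | 83.7% | 73.3% | 86.8% (40) |
| 20% | 74.4% | 54.3% | 83.1% (36) |
| 30% | 62.9% | 38.2% | 77.0% (31) |

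**5. When restriction would not help.** Suppose users show a fraction g of the effect. At k = 1 the ratio becomes (1 − f + f g)² / (1 − f). With g = 1 this is 1/(1 − f): 1.11 at f = 10% and 1.25 at f = 20%, so pooling is then better. The ratio equals 1 when g = [√(1 − f) − (1 − f)] / f. At f = 20% that is (0.894 − 0.800)/0.2 = 0.47. With equal SDs, restriction therefore gains information only if users show less than about half of the effect; a larger SD in users raises that threshold.

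**The case against.** Several objections have force.

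- **The text contains no contradiction, and the full protocol is not shown.** Section 2.1 cites a version 4.0 protocol, and 2.9 is one paragraph that does not list its covariates. Handling of insulin use may be specified there. That stands as a caution. But the article does state its eligibility rules, prohibited drugs, outcomes and analysis sets, and followed as written they give a mixed comparison.
- **No assay is named.** A reader might infer that the laboratory will certainly measure injected insulin, and that the outcome therefore fails to measure own insulin. The article supports neither step. Detection depends on an unnamed assay and on the product, and the outcome remains sound in non-users.
- **The outcome is worded as insulin levels within a glucose profile**, not as endogenous secretion. That is true. The dilution argument rests on the stated purpose in section 3, not on a declared measure of secretion.
- **Systematic bias is limited.** Randomization, change from baseline and the exclusion of patients who switched glucose-lowering drugs all help. A reader might also infer that chance imbalance in users between arms would create a false difference, but such chance is what the 0.05 level covers. The main harm is lost power. One reservation remains: the trial is open-label and the article states no rule on changes of insulin treatment after randomization, so such changes could differ by arm.
- **Long diabetes duration does not show how many users will enrol.** It is one of five alternative risk factors, so the share is unknown.
- **The large losses rest on assumed SD ratios of 2 to 4 and no effect in users.** This stands, so the equal-SD figures carry the point and the rest is a range.

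**Conclusion.** The point holds in a limited form. The published rules admit insulin-treated patients and compare insulin levels in sets not restricted by insulin use, so the pooled result may mix injected with own insulin. For the question in section 3 the comparison is then diluted and noisier, though not void.

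If users show no effect and vary no more than non-users, 90% to 70% of the non-users' information is kept at shares of 10% to 30%. At double the SD it is 69% to 37%. The share of users, the SD ratio and the absence of effect in users are all assumptions, and if users respond as non-users do, there is no loss.

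This is a cheap improvement to one group of secondary outcomes, not a fault in the trial's main comparison.

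**What to change.** In 2.6 and 2.9, define the fasting and postprandial insulin analysis in patients not receiving exogenous insulin at baseline (Visit 3, before randomization). Show baseline users descriptively. Keep patients who start insulin after randomization in the analysis, and list those starts by arm.

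The restriction should not use insulin status at Visit 4. That status arises after randomization in an open-label trial. If one drug worsened glycaemia, dropping the patients who start insulin would remove them selectively and break the randomized comparison. Keeping them leaves some injected insulin in the follow-up values, which the list by arm makes visible.

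The cost is one sentence in the analysis, insulin use recorded at baseline and starts recorded during follow-up if they are not already captured, and a smaller number for these outcomes (for example 36 instead of 45 per arm at an assumed 20% share). No extra sampling is needed.
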